# Synopsis of the Study Protocol

| Study Title | A Phase II Clinical Study to Evaluate the Efficacy and Safety of Afatinib for Pretreated Patients with Advanced Esophageal Squamous Cell Carcinoma with EGFR Overexpression/Amplification |
| --- | --- |
| Study Objective | To explore the efficacy and safety of afatinib as the second-line or beyond therapy for advanced esophageal squamous cell carcinoma (ESCC) with EGFR overexpression/amplification |
| Trial Site | Peking University Cancer Hospital and Institute |
| Trial Design | A non-randomized, open-label, single-arm clinical study. Subjects receive afatinib (40 mg po. Qd) in 4-week cycles until disease progression, occurrence of intolerable toxicity, loss to follow-up or death, or other situations in which the investigator determines the treatment should be discontinued. |
| Number of Subjects | 40 |
| Study Endpoints | Primary study endpoint: Objective response rate (ORR)  Secondary study endpoints: Disease control rate (DCR), safety, progression Free Survival (PFS) and overall survival (OS)  Exploratory endpoint: Quality of life, efficacy markers |
| Study Duration | First Patient In Time (FPI): 05/2019  Last Patient In Time (LPI): 05/2020 |
| Inclusion Criteria | 1. Voluntarily participating and signing the Informed Consent Form; 2. Age: 18 to 70 years of age; 3. Male or female; 4. Pathologically confirmed ESCC; 5. Pathologically confirmed immunohistochemical EGFR (3+) or EGFR-FISH amplification or EGFR amplification by NGS-testing (see Annex 4 for specific testing standards) 6. Radiographically confirmed unresectable advanced ESCC; 7. Failure of the first-line or beyond therapy; 8. At least one measurable lesion (per RECIST 1.1 criteria), with the imaging diagnosis ≤ 21 days apart from the enrollment time; 9. Life expectancy of ≥ 3 months; 10. General performance status (ECOG) score of 0-2; 11. Sufficient bone marrow hematopoiesis (within 7 days): hemoglobin ≥ 9 g/dL, white blood cell ≥ 3.0 × 10^9^/L, neutrophil ≥ 1.5 × 10^9^/L, platelet ≥ 100 × 10^9^/L; normal hepatic and renal functions (within 14 days): TBIL ≤ 1.5 × upper limit of normal (ULN); ALT and AST ≤ 2.5 × ULN, or ≤ 5 × ULN in the presence of liver metastasis; creatinine ≤ 1.5 × ULN; 12. Cardiac, pulmonary, renal and hepatic functions are basically normal; |
| Exclusion Criteria | 1. Patients who are currently receiving other effective treatment regimens; 2. Participation in other clinical trials within 4 weeks prior to enrollment; 3. Inability to cooperate in oral administration of afatinib; 4. No measurable tumor lesion, for example, body cavity fluid or diffuse organ infiltration; 5. Prior radiotherapy on the measurable lesion; 6. Coexistence of other primary malignancies other than esophageal cancer, excluding cured basal cell carcinoma of skin and cervical carcinoma in situ; 7. Clinically significant cardiovascular diseases such as heart failure (NYHA class III-IV), uncontrolled coronary heart disease, cardiomyopathy, arrhythmia, uncontrolled hypertension, or history of myocardial infarction within the past 1 year; 8. Nervous or mental disorders affecting the cognitive ability, including central nervous system metastasis; 9. Severe active clinical infection (at grade >2 per NCI-CTCAE Version 4.0) including active tuberculosis within 14 days prior to enrollment; 10. Known or self-complained HIV infection or active hepatitis B or hepatitis C; 11. Uncontrolled systemic diseases such as poorly uncontrolled diabetes mellitus; 12. History of interstitial lung disease such as interstitial pneumonia and pulmonary fibrosis, or chest X-ray/CT evidence of interstitial lung disease at baseline; 13. Keratitis, ulcerative keratitis or severe xerophthalmia; 14. Known hypersensitivity or allergic reaction to any component of the investigational drug; 15. Pregnancy (confirmed by serum β-chorionic gonadotrophin test) or lactation; |
| Treatment Regimen | Afatinib (40 mg Po Qd) therapy in 4-week cycles, until disease progression, occurrence of intolerable toxicity, loss to follow-up or death, or other situations in which the investigator determines the treatment should be discontinued.  Dose adjustment: If a patient cannot tolerate the treatment due to adverse drug reaction, afatinib will be paused until recovering to grade 1 or less, with dose reduction by 10 mg decrements to a minimum dose of 20 mg. |
| Outcome Measures | 1. Efficacy evaluation according to the Response Evaluation Criteria in Solid Tumors (RECIST) 1.1, including CR, PR, SD, PD. ORR (CR+PR), DCR (CR+PR+SD) 2. Efficacy evaluation timepoints: Baseline investigations, specifically, spiral CT or MRI examination (which should remain consistent in subsequent efficacy evaluations), will be done within 3 weeks before treatment, and efficacy evaluation will be performed once at Weeks 4, 8 post-dose, respectively and thereafter once every 8 weeks. In case of disease progression, intolerable toxicity or patient-requested withdrawal, the patient will be allowed to withdraw from the clinical trial. 3. The time window of efficacy evaluation is +/-1 week. |
| Safety and Quality of Life Evaluation | 1. The safety of the investigational drug will be evaluated by recording, reporting and analyzing subjects’ adverse events, vital signs, laboratory tests and other physical examinations. 2. Adverse events will be evaluated according to National Cancer Institute-Common Terminology Criteria for Adverse Events (NCI-CTCAE) Version 4.0 (published on June 14, 2010). 3. The quality of life will be evaluated using EORTC quality of life questionnaires QLQ-C30, QLQ-OES18. |
| Statistical Analysis | All data, including demographics, baseline, various efficacy evaluation indicators and all safety data, etc., will be analyzed by R 3.6.1. |
| Sample Size Calculation | Simon 2-stage design  Power = 0.8; α = 0.05  P_0_ = 0.10, P_1_ = 0.25  Stage 1: N_1_ = 22, R_1_ = 2  Stage 2: N_total_ = 40, R_2_ = 8 |

**A Phase II Clinical Study to Evaluate the Efficacy and Safety of Afatinib for Pretreated Patients with Advanced Esophageal Squamous Cell Carcinoma with EGFR Overexpression/Amplification**

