# III. Overall Design of the Study

This study is a non-randomized, open-label, single-arm clinical study. Subjects receive afatinib (40 mg po. Qd) in 4-week cycles until disease progression, occurrence of intolerable toxicity, loss to follow-up or death, or other situations in which the investigator determines the treatment should be discontinued.

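### The Simon bounds R1 = 2 and R2 = 8 are printed without a definition; in the usual Simon notation they give 69% power, not the stated 80%, and the action at 2/22 and at 8/40 is left open

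*Protocol*

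**What the plan says.** The Sample Size Calculation row of the protocol synopsis names a "Simon 2-stage design" with "Power = 0.8; α = 0.05" and "P_0_ = 0.10, P_1_ = 0.25". The bounds follow as "Stage 1: N_1_ = 22, R_1_ = 2" and "Stage 2: N_total_ = 40, R_2_ = 8". The primary endpoint is the objective response rate (ORR).

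The row does not say whether R is the largest count that stops or fails the trial, or the smallest count that lets it continue or succeed. It does not say whether the design is the minimax or the optimal one.

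No other section helps. Section III says "This study is a non-randomized, open-label, single-arm clinical study" and mentions neither stages nor a rule for stopping after the first 22 patients. Section 10.3 names the software and the safety population but not the design.

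**The concern.** These two numbers are the protocol's only decision thresholds for the primary endpoint. In a design called Simon two-stage, a statistician will usually read r1 and r as the largest counts that lead to stopping or to a negative conclusion. On that reading the printed pair contradicts the power stated in the same row.

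Two results are affected:

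- **2 responders of 22 at stage 1.** Depending on the reading, recruitment stops or 18 more patients are treated.
- **8 responders of 40 at the end (ORR 20%).** Depending on the reading, the drug is declared active or not.

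Neither result is a remote possibility. Because the trial is open-label, a threshold that is not fixed in words could also be interpreted after the responses are known.

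**Working it through.** **Inputs, all from the Sample Size Calculation row of the synopsis:** p0 = 0.10, p1 = 0.25, alpha = 0.05, power = 0.80, n1 = 22, N = 40 (so 18 patients in stage 2), R1 = 2, R2 = 8. Sidedness is not stated; a Simon design is one-sided, and that is assumed here.

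**Formula.** Let the trial stop if X1 ≤ r1 and fail if the total is ≤ r. Then

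P(success | p) = Σ over x from r1 + 1 to 22 of Bin(x; 22, p) × P(Bin(18, p) ≥ r + 1 − x).

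Alpha is this sum at p = 0.10, and power is the sum at p = 0.25. The chance of early stopping under p0 is PET = P(Bin(22, 0.10) ≤ r1). The expected sample size under p0 is 22 + 18 × (1 − PET).

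**Reproducing the stated design.** A full search over n1, r1, N and r, with N from 25 to 55, alpha ≤ 0.05 and power ≥ 0.80, gives a smallest N of 40. The design at N = 40 with the lowest expected size under p0 has n1 = 22, r1 = 2 and r = 7. This minimax design matches the printed N1, R1 and N exactly and differs from the printed R2 by one. The optimal design for the same inputs is 2/18, 7/43, so it is not the one printed.

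**Operating characteristics under each reading of the printed numbers**

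| Reading | r1, r | Alpha | Power | PET under p0 | Expected N under p0 |
|---|---|---|---|---|---|
| Both R are largest failing counts: stop ≤2/22, fail ≤8/40 | 2, 8 | 0.0151 | 0.6930 | 0.620 | 28.8 |
| R1 largest stopping count, R2 smallest success count: stop ≤2/22, success ≥8/40 | 2, 7 | 0.0398 | 0.8032 | 0.620 | 28.8 |
| Both R are smallest passing counts: continue ≥2/22, success ≥8/40 | 1, 7 | 0.0416 | 0.8161 | 0.339 | 33.9 |
| R1 smallest continuing count, R2 largest failing count: continue ≥2/22, fail ≤8/40 | 1, 8 | 0.0155 | 0.6994 | 0.339 | 33.9 |

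Only the two readings that count 8/40 as a success reach 0.80.

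**Weight of the two boundary results**

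- Exactly 2/22 has probability 0.620 − 0.339 = 0.281 at p = 0.10. At p = 0.25 it is Bin(2; 22, 0.25) = 0.046.
- Ending at exactly 8/40 after passing stage 1 with at least 3 responders has probability 0.8032 − 0.6930 = 0.110 at p = 0.25. At p = 0.10 it is 0.0398 − 0.0151 = 0.025.

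Under the first reading, 80% power would need a true ORR of about 27.4% rather than 25%.

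**The case against.** The strongest reply is that nothing has been miscalculated. The row does not call R a rejection bound, so the 69% depends on a definition that the reader brings to it. The stated alpha and power can serve as a key: they rule out both readings in which 8/40 fails, and both remaining readings make 8/40 a success. One shared convention, with both numbers as minimum counts, meets the stated targets. It is not the minimax design, but the protocol does not claim to use that one. The statistical analysis plan, which is not shown, may put the rule in words.

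Much of this stands. A reader might infer that the trial is underpowered. The protocol does not support that: N = 40 is the smallest total that meets the stated inputs. A reader might also infer that the two bounds must follow different conventions. That is the likelier origin, because the other three numbers match the minimax design exactly, but it is not proven.

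The reply does not remove the point. Recovering the final threshold requires recomputing the design and discarding the notation most readers would apply. The stated alpha and power cannot settle the action at 2/22 at all, since both 0.803 and 0.816 satisfy them. That action governs whether recruitment continues, so it belongs in the protocol, which already prints the bounds. On the other hand, the 2/22 ambiguity mainly affects early stopping of an inactive drug: if 8/40 counts as success, alpha is at most 0.042 either way.

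**Conclusion.** The point holds as a defect in the printed bounds, not in the sample size. R1 and R2 are undefined. In the usual Simon notation they give alpha 0.015 and power 0.693, which conflicts with the stated 0.80 and makes 8/40 a negative result. The stated power requires 8/40 to be a success. What happens at 2/22 remains open, and with it the chance of stopping early for an inactive drug: 0.62 or 0.34, an expected 28.8 or 33.9 patients under p0.

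The likeliest explanation is that R2 is a success minimum printed beside a Simon-type R1. This is an inference from the match with the minimax design. The figures assume a one-sided test, exact binomial probabilities, and all 22 and 40 patients counted in the denominators. The protocol needs correcting because these are its only decision thresholds for the primary endpoint.

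**What to change.** State the rule with inequalities in the Sample Size Calculation row of the synopsis and repeat it in Section III.

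If the minimax design is meant, suitable text is: *Stage 1: stop if ≤2 of 22 patients respond; continue if ≥3 respond. Stage 2: of 40 patients, conclude insufficient activity if ≤7 respond (r = 7) and sufficient activity if ≥8 respond. Exact one-sided alpha 0.040, power 0.803.*

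If another rule is meant, print it with its own figures:

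- continue with ≥2/22 and succeed with ≥8/40: alpha 0.042, power 0.816, early stopping under p0 0.34;
- stop with ≤2/22 and fail with ≤8/40: alpha 0.015, power 0.69, replacing the stated 0.80.

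The cost is a few lines of text. The first two rules need no extra patients and keep the stated power. The third keeps N = 40 only by accepting 69% power. The wording should be fixed before the stage 1 responses are reviewed.

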# I. Background of the Study

The morbidity and mortality of esophageal cancer rank 12^th^ and 7^th^, respectively in the global scale. In China, the morbidity and mortality of esophageal cancer rank 6^th^ and 4^th^, respectively, with both the diagnosed cases and death cases reaching 50% of the total in the world, and more than 90% of esophageal cancer are squamous cell carcinoma. The prognosis of esophageal cancer is extremely poor, 70% of patients are at advanced stage of the disease when diagnosed, and their 5-year survival rate is 20% ^[1]^. Traditional cytotoxic chemotherapies for advanced esophageal squamous cell carcinoma (ESCC) is platinum-based. In our center, the combination of paclitaxel and cisplatin as first-line chemotherapy had an objective response rate of 48.6%, a median progression-free survival (mPFS) of 7 months, and a median overall survival (mOS) of 13 months ^[2]^. Esophageal cancer patients who have tumor progression within 6 months after first-line platinum-based chemotherapy cannot receive platinum-based treatment in the second-line therapy as they are considered as resistant to platinum. For such platinum-resistant patients, second-line chemotherapy has a relatively low response rate. Burkart *et al.* reported that, the ORR of irinotecan in cisplatin-refractory advanced esophageal cancer was less than 15% ^[3]^. According to unpublished retrospective data from Gastrointestinal Department of Beijing Cancer Hospital, in the second-line therapy of esophageal cancer using irinotecan, fluorouracil or gemcitabine, etc., the ORR was only 12.8%, mPFS 3.5 months, and mOS 9.3 months. Other than cytotoxic chemotherapy, targeted therapy and immunotherapy are also the hot spots of current research; however, targeted therapy of ESCC has not yet been supported with any positive results from phase III clinical studies and the onset of effect in immunotherapy takes a relatively long time, suggesting neither of them is applicable to patients who develop primary drug resistance rapidly.

Gefitinib, erlotinib and afatinib are small-molecule EGFR tyrosine kinase inhibitors (EGFR-TKIs) that competitively bind to EGFR via endogenous ligands, inhibits the activation of tyrosine kinase and subsequently blocks EGFR signaling pathway to inhibit the proliferation and metastasis of tumor cells and promote their apoptosis. NCCN guidelines recommend the use of the EGFR-TKIs mentioned above as the first-line therapy for EGFR-mutant non-small cell lung cancer ^[4]^. Among them, afatinib is an irreversible dual inhibitor targeting EGFR and human epidermal growth factor receptor 2 (HER2) tyrosine kinases. It has been demonstrated in LUX-Lung 3 and LUX-Lung 6 studies that, compared to chemotherapy, afatinib significantly prolonged the progression-free survival of patients with EGFR-mutant non-small cell lung cancer and significantly reduced the risk of death ^[5, 6]^. In terms of safety, the study results of LUX-Lung 3, LUX-Lung 6 and LUX-Lung 7 showed that, adverse reaction related therapy discontinuation occurred in 8%, 6.3%, and 6.3% of patients, respectively ^[5-7]^. In addition, after dose adjustment of afatinib, adverse reactions were reduced with no influence on the efficacy.

In ESCC, the reported epidermal growth factor receptor (EGFR) overexpression rate is 30-50% and the EGFR amplification rate about 7-13%. Studies have shown that, EGFR overexpression is a contributor to the poor prognosis of esophageal cancer ^[8-11]^. In ESCC, patients with high EGFR expression or those with EGFR amplification can benefit from gefitinib ^[12, 13]^. In EGFR-FISH positive esophageal cancer, overall survival was improved with gefitinib compared with placebo (HR 0.59; 95%CI 0.35-1.00, P = 0.05), and patients with EGFR amplification gained greater benefit from gefitinib (HR 0.21; 95%CI 0.07-0.64, P = 0.006). In preclinical study, afatinib achieved the best efficacy in PDX models with EGFR overexpression, especially EGFR amplification ^[14]^. So far, there have been no clinical study reports on the efficacy and safety of afatinib in treating ESCC.

Based on the study background above, this study explores the efficacy and safety of afatinib for pretreated patients with advanced ESCC with EGFR overexpression/amplification and provides advanced ESCC patients with more evidence-based medical proof through prospective exploration with a small sample size.

# II. Study Objective

To explore the efficacy and safety of afatinib for pretreated patients with advanced ESCC with EGFR overexpression/amplification.

# III. Overall Design of the Study

This study is a non-randomized, open-label, single-arm clinical study. Subjects receive afatinib (40 mg po. Qd) in 4-week cycles until disease progression, occurrence of intolerable toxicity, loss to follow-up or death, or other situations in which the investigator determines the treatment should be discontinued.

# IV. Case Selection

## (I) Inclusion Criteria

- - - 1. Voluntarily participating and signing the Informed Consent Form (ICF);
      2. Age: 18 to 70 years of age;
      3. Male or female;
      4. Pathologically confirmed ESCC;
      5. Pathologically confirmed immunohistochemical EGFR (3+) or EGFR-FISH amplification or NGS-testing EGFR amplification
      6. Radiographically confirmed unresectable advanced ESCC;
      7. Failure of the first-line or beyond therapy;
      8. At least one measurable lesion (per RECIST 1.1 criteria) or evaluable but non-measurable lesion, with the imaging diagnosis ≤ 21 days apart from the enrollment time;
      9. Life expectancy of ≥ 3 months;
      10. General performance status (ECOG) score of 0-2;
      11. Sufficient bone marrow hematopoiesis (within 7 days): hemoglobin ≥ 9 g/dL, white blood cell ≥ 3.0 × 10^9^/L, neutrophil ≥ 1.5 × 10^9^/L, platelet ≥ 100 × 10^9^/L; normal hepatic and renal functions (within 14 days): TBIL ≤ 1.5 × upper limit of normal (ULN); ALT and AST ≤ 2.5 × ULN, or ≤ 5 × ULN in the presence of liver metastasis; creatinine ≤ 1.5 × ULN;
      12. Cardiac, pulmonary, renal and hepatic functions are basically normal;

## (II) Exclusion Criteria

1. Patients who are currently receiving other effective treatment regimens;
2. Participation in other clinical trials within 4 weeks prior to enrollment;
3. Inability to cooperate in oral administration of afatinib;
4. No measurable tumor lesion, for example, body cavity fluid or diffuse organ infiltration;
5. Prior radiotherapy on the measurable lesion;
6. Prior use of anti-EGFR targeted therapy;
7. Coexistence of other primary malignancies other than esophageal cancer, excluding cured basal cell carcinoma of skin and cervical carcinoma in situ;
8. Clinically significant cardiovascular diseases such as heart failure (NYHA class III-IV), uncontrolled coronary heart disease, cardiomyopathy, arrhythmia, uncontrolled hypertension, or history of myocardial infarction within the past 1 year;
9. Nervous or mental disorders affecting the cognitive ability, including central nervous system metastasis;
10. Severe active clinical infection (at grade >2 per NCI-CTCAE Version 4.0) including active tuberculosis within 14 days prior to enrollment;
11. Known or self-complained HIV infection or active hepatitis B or hepatitis C;
12. Uncontrolled systemic diseases such as poorly uncontrolled diabetes mellitus;
13. History of interstitial lung disease such as interstitial pneumonia and pulmonary fibrosis, or chest X-ray/CT evidence of interstitial lung disease at baseline;
14. Keratitis, ulcerative keratitis or severe xerophthalmia;
15. Known hypersensitivity or allergic reaction to any component of the investigational drug;
16. Pregnancy (confirmed by serum β-chorionic gonadotrophin test) or lactation;

## (III) Removal Criteria

1. Non-compliance with inclusion criteria;
2. Patients who violate the requirements of the study protocol, fail to take medicines as required and fail to complete the plan;
3. Poor quality of data recording, and incomplete and inaccurate data.
4. Use of other antitumor drug therapy during the clinical study period.

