- All patients included in the study must be assessed for response to treatment, even if there are major trial protocol treatment deviations or if they are ineligible. Each patient will be assigned one of the following categories: 1) complete response, 2) partial response, 3) stable disease, 4) progressive disease, 5) early death from malignant disease, 6) early death from toxicity, 7) early death because of other cause, or 9) unknown (not assessable, insufficient data).
- All of the patients who met the eligibility criteria should be included in the main analysis of the response rate. Patients in response categories 4-9 should be considered as failing to respond to treatment (disease progression). Thus, an incorrect treatment schedule or drug administration does not result in exclusion from the analysis of the response rate. Precise definitions for categories 4-9 will be protocol specific.
- All conclusions should be based on all eligible patients.
- Sub-analyses may then be performed on the basis of a subset of patients, excluding those for whom major protocol deviations have been identified (e.g., early death due to other reasons, early discontinuation of treatment, major protocol violations, etc.). However, these sub-analyses may not serve as the basis for drawing conclusions concerning treatment efficacy, and the reasons for excluding patients from the analysis should be clearly reported.
- The 95% confidence intervals should be provided.

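### Removal Criteria 2–4 take cases out for events after enrolment, while Annex 2 keeps all eligible patients in the main response-rate analysis; the primary ORR denominator is left in conflict

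*Protocol*

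**What the plan says.** Section IV (III), Removal Criteria, has four items. Item 1 concerns patients who do not meet the inclusion criteria. The other three can be known only once a patient is on study:

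- item 2: "Patients who violate the requirements of the study protocol, fail to take medicines as required and fail to complete the plan"
- item 3: "Poor quality of data recording, and incomplete and inaccurate data"
- item 4: "Use of other antitumor drug therapy during the clinical study period", with no restriction to the time before progression.

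Reasons for stopping study treatment are listed separately, in Section IV (IV), Termination Criteria.

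Annex 2, under the reporting of results, gives its own rule for the response rate: "All of the patients who met the eligibility criteria should be included in the main analysis of the response rate". It continues: "Thus, an incorrect treatment schedule or drug administration does not result in exclusion from the analysis of the response rate". It classes patients who are not assessable or have insufficient data among those who failed to respond. It allows analyses that leave out patients with major deviations, but not as a basis for efficacy conclusions.

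Section 10.3 names one population, patients who received at least one dose, and only for safety. ORR is the primary endpoint. The Synopsis tests it in a Simon two-stage design with "Power = 0.8; α = 0.05", "P_0_ = 0.10, P_1_ = 0.25" and "Stage 1: N_1_ = 22, R_1_ = 2", then 40 patients in total with R2 = 8.

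**The concern.** Two analysts, one following the Removal Criteria and one following Annex 2, could report different primary results from the same data, and the choice between them could be made after responses are known.

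The difference is unlikely to be neutral. A patient with no usable follow-up scan, or one moved to another antitumor drug, is more likely to be a non-responder than a responder. Taking such patients out of the denominator pushes the reported ORR upwards. In a single-arm trial of 40 patients judged against a fixed 10% null rate, a few removals change the estimate visibly. If removed patients were also replaced, the trial would be testing a selected group against a null rate meant for all eligible patients.

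**Working it through.** **1. The rules side by side.**

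| Event after enrolment | Removal Criteria | Annex 2, main response-rate analysis |
|---|---|---|
| Protocol violation or non-compliance (item 2) | case removed | kept; wrong schedule or administration is no ground for exclusion |
| Incomplete data (item 3) | case removed | kept; not assessable counts as failure |
| Other antitumor drug (item 4) | case removed | kept if eligible |

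Item 1 does not conflict, because Annex 2's main analysis is itself limited to eligible patients. Annex 2 also does not turn every deviator into a failure: a confirmed responder who deviates later remains a responder.

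**2. The plan's own design.** Inputs from the Synopsis: p0 = 0.10, p1 = 0.25, n1 = 22, r1 = 2, N = 40, R2 = 8. Continue if stage 1 has more than 2 responses, and take success as 8 or more in total:

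P(success | p) = Σ over x = 3 to 22 of Bin(x; 22, p) × P(Y ≥ 8 − x), with Y ~ Bin(18, p).

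- p = 0.10: 0.0398
- p = 0.25: 0.8032

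This meets the stated alpha and power. If R2 = 8 instead means that success needs more than 8, the values are 0.0151 and 0.693. The power target then fails, so 8 or more is the reading that fits, but the protocol does not say so. Both are carried forward.

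**3. Effect on the reported ORR.** If a share d is removed and all are non-responders, ORR is multiplied by 1/(1 − d). With 8 responders:

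- none removed: 8/40 = 20.0% (exact 95% CI 9.1–35.6%)
- 4 removed: 8/36 = 22.2%
- 8 removed: 8/32 = 25.0% (11.5–43.4%), which equals P1

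**4. Effect on type I error if removed patients are replaced up to 22 and 40.** The protocol gives neither a removal share nor a replacement rule, so d and replacement are assumptions. At a true ORR of 10% among all eligible patients, the rate among those kept is 0.10/(1 − d), put into the formula in step 2:

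| d | Rate among kept | Success at ≥8 | Success at >8 |
|---|---|---|---|
| 0 | 0.100 | 0.040 | 0.015 |
| 10% | 0.111 | 0.067 | 0.028 |
| 15% | 0.118 | 0.087 | 0.039 |
| 20% | 0.125 | 0.114 | 0.054 |

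**5. Without replacement.** Removing only non-responders leaves the responder count unchanged at both stages. The comparison with 8 responses gives the same answer, and only the percentage and its interval move.

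**The case against.** The strongest reply is that the Removal Criteria are a bare list under Case Selection and name no analysis set, endpoint or denominator. Section XI refers to a statistical plan, which could apply Annex 2 to ORR and use the removal list for a per-protocol set. It is true that exclusion from the ORR denominator is an inference. It is the sensible one: stopping treatment has its own list, and poor data recording is not a reason to stop a drug. The conflict also lies within the protocol, whatever a later plan may say.

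A reader might infer that item 2 mostly catches patients who stop for toxicity, progression or death. The text does not support that. Section III and the Dosage Regimen make those events planned ends of treatment, so such patients have followed the plan, and item 2 can be read as non-compliance only.

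A reader might also infer that OS loses everyone who goes on to a next line of therapy. That needs the widest reading of item 4. Its study period could equally mean time on study treatment, in line with the ban on concomitant antitumor therapy under Prohibited Medications. The wording leaves both readings open.

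Finally, it is tempting to say that the Simon error rates are broken. Step 5 shows that this does not follow without replacement, and the protocol has no replacement rule. Under the stricter reading of R2 = 8, even with replacement, type I error passes 0.05 only at 20% removed among the shares tabulated.

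**Conclusion.** The conflict stands and bears on the primary endpoint. Removal items 2 and 3, and item 4 read literally, cannot be followed together with Annex 2's rule for the response rate, and Section 10.3 does not resolve it.

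The expected direction is a higher reported ORR. That rests on removed patients being mostly non-responders, which is likely but not certain. The size depends on how many are removed: 8 of 40 would move 20% to 25%.

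Type I error inflation to 0.067–0.114 rests on four assumptions together: 10–20% removed, all of them non-responders, replacement up to 40, and success at 8 or more responses. With success above 8 the range is 0.028–0.054. Without replacement the decision at 8 or more responses is unaffected. Distortion of OS follows only if item 4 covers therapy after progression.

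**What to change.** State one primary ORR population that follows Annex 2:

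- The denominator is all eligible enrolled patients, with eligibility judged only on facts fixed before the first dose. The Simon stages use the 22 and 40 patients so defined, without replacement.
- Patients with no evaluable post-baseline assessment count as non-responders. Confirmed responders who deviate later remain responders.
- Removal items 2–4 serve only to define a supportive per-protocol or sensitivity set, and are not applied to PFS or OS.

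The cost is protocol wording only. The reported ORR may be lower than it would be under the removal list.
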